### Statistical methods

All data obtained at baseline will be given a coded ID-number before they are used in further statistical analyses. After double data entry and with the guidance of a statistician, statistical analysis will be performed in SPSS. Stratification for relevant confounders will be performed and descriptive statistics as well as multivariate analyses will be conducted. Ordinal scaled data will be evaluated as to a Gaussian distribution after which between-group differences will be tested in accordance by the use of *t*-test or non-parametric test. Dichotomous efficacy variables are tested by use of chi^2^ test or exact test in case of small numbers. The significance level will be a p-value of less than 0.05.

The final number of patients included in the trial will be reported and intention-to-treat analyses are to be performed meaning all participants will be included in the analysis irrespective of compliance with the intervention protocol. However, an additional per-protocol analysis will also be conducted. Data from patients who refused to participate, dropouts, and loss-to-follow-up participants will be entered to an analysis based upon demographics in order to consider selection bias when interpreting the results. The presentation of the trial results will be according to the CONSORT statement to Trials of Nonpharmacologic Treatment 
[47].

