### Randomisation

Patients, who fulfil the inclusion criterions, are included consecutively in the trial depending of time of their referral to the dermatologist. A baseline objective evaluation of hand eczema severity is carried out prior to the individual randomisation, which is performed centrally at the National Allergy Research Centre using a computer-generated algorithm unknown to the investigator. The patients are allocated to the intervention group, or conventional information in the control group. The percentage of patients allocated to each group is approximately 50:50. Randomisation is stratified by blocks according to setting and gender, the latter because of a gender ratio of hand eczema, as women have the double risk of men of hand eczema. Also, gender has been shown to impact both performed self-management 
[24] and ‘prescribed’ self-management 
[25].

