### Trial intervention

The trial aims at intervening multi modally through initiatives which separately may be expected to support patient self-management and to be beneficial to the hand eczema prognosis 
[10,13,15,27-29]. The intervention is named The Healthy Skin Clinic in order to emphasise that self-management of hand eczema is more than medication adherence thus also involves health promotion. The Healthy Skin Clinic complies with usual clinical practice aiming to provide the patient with a systematic, yet individually, based counselling programme including a support module. The Healthy Skin Clinic is maintained by experienced nurses within the dermatological specialty along with the investigator (setting A), or by an experienced health care assistant supervised by the investigator and a dermatologist (setting B). A high level of team communication is conducted in order to provide commonality of the intervention.

The intervention is founded upon three concurrent elements. Firstly, a SKIN-profile is generated by responses from the baseline questionnaire. The profile is descriptive of the patient regarding susceptibility; knowledge; co-morbidity; social support; and necessary precautions i.e. allergies and aggravating irritant factors. One significant purpose of generating the profile is to clarify the multifactorial aetiology of (the persistence of) chronic hand eczema thus direct focus to the relevant areas in the following nurse-led consultation.

Secondly, a patient self-management book is offered. The book is a dynamic tool, which is launched in an electronic form, i.e. a secure website. Patients, with no possibilities of using information technology, will be handed over a physical book containing the same features. The patient self-management book contains information material which is tailored to the SKIN-profile. In addition, tools for self-monitoring of the disease are offered with the purpose of encouraging the patient to take a more proactive role in the course.

Finally, in addition to the nurse-led consultation, support to self-management through asynchronous communication and networking is offered. The online users may facilitate contact to either the intervention team or to other trial participants by use of the website. To the users of the physical self-management book a telephone based hotline is offered. An overall graphical depiction of the Healthy Skin Clinic intervention is presented in Figure 

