#### Possible confounders

Several factors might affect self-management capabilities and the prognosis of disease thus are included in the questionnaire i.e. socio-economic status; perceived social support as well as depression and stress. In the data analysis a rough assessment of prevalent depression among participants is done by items included in the mental health sub-scale in SF-36 
[42].

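### Randomisation is stratified by setting and gender, but the named between-group tests carry neither factor; the effect is mildly conservative and costs nothing to remove

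*Protocol article*

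**What the plan says.** Under Randomisation, the protocol article states that "Randomisation is stratified by blocks according to setting and gender", after a baseline HECSI assessment and with allocation close to 1:1. For gender it gives reasons: women's higher risk of the disease, and that "gender has been shown to impact both performed self-management" as well as the self-management that is prescribed. It gives no reason for setting.

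Under Statistical methods, scored data are checked for a Gaussian distribution, after which "between-group differences will be tested in accordance by the use of" a t-test or a non-parametric test. Dichotomous outcomes get a chi-square test, or an exact test when numbers are small. Neither setting nor gender appears in these tests. The same section says: "Stratification for relevant confounders will be performed and descriptive statistics as well as multivariate analyses will be conducted". It does not name the covariates or say whether the simple tests or the adjusted analyses are primary.

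Possible confounders lists "socio-economic status; perceived social support as well as depression and stress". Setting, gender and baseline HECSI are not in that list, and the list is not declared to be the adjustment set.

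**The concern.** Blocking within strata forces the arms to be nearly balanced on setting and gender. If these factors predict the outcome, the treatment difference then varies less from trial to trial than a plain two-sample test assumes. That test still counts the between-stratum variation as noise, so its standard error is too large, its intervals are too wide and its true size is below the nominal 5%. The precision gained by stratifying is used only if the analysis includes the strata.

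As written, the only tests the article names are unstratified. Where the strata might enter, in the stratified or multivariate analyses, the text neither says that they will nor gives those analyses primary status.

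**Working it through.** The article gives no figure on this point, so there is none to reproduce.

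**Inputs**
- Strata: 2 settings × 2 genders = 4, blocked, about 1:1 (Randomisation).
- Significance level: 5% (Statistical methods), taken as two-sided because sidedness is not stated.
- Six-month HECSI: means 11 and 7.7, SDs 9.0 and 6.0, 150 per group (sample size section). Difference = 3.3.
- R², the share of outcome variance explained by setting and gender: not given. **Assumed** range 0 to 0.20.

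**Size and interval width.** After stratified blocks, the true SE of the unadjusted difference is about √(1−R²) times the SE that the t-test reports. Hence:
- actual size = 2[1 − Φ(1.96/√(1−R²))]
- excess interval width = 1/√(1−R²) − 1

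For R² = 0.10: 1.96/√0.90 = 2.066, so size = 3.9%; and 1/√0.90 = 1.054, so intervals are 5.4% too wide.

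**Power at 150 per group.** Pooled SD = √((81+36)/2) = 7.65, so SE = 7.65 × √(2/150) = 0.883.
- Unadjusted: Φ[(3.3 − 1.96×0.883)/(0.883√(1−R²))]
- Adjusted for strata: Φ[3.3/(0.883√(1−R²)) − 1.96]

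| Assumed R² | Actual size | CI coverage | Excess width | Power, unadjusted | Power, adjusted |
|---|---|---|---|---|---|
| 0 | 5.0% | 95.0% | 0% | 96.2% | 96.2% |
| 0.05 | 4.4% | 95.6% | 2.6% | 96.6% | 97.0% |
| 0.10 | 3.9% | 96.1% | 5.4% | 96.9% | 97.6% |
| 0.20 | 2.8% | 97.2% | 11.8% | 97.6% | 98.7% |

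The power differences are 0, 0.4, 0.7 and 1.1 points. If only 87 per group were analysed, the same formulas give 82.5% against 85.1% at R² = 0.10, and 83.9% against 88.9% at R² = 0.20.

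**Check by simulation.** Settings: 300 patients, four strata, assumed block size 4, equal settings, two-thirds women, normal outcome, 8,000 null runs for each R². For R² = 0, 0.05, 0.10 and 0.20, the rejection rates were:
- t-test: 5.0%, 4.7%, 3.8%, 2.7%
- Mann-Whitney test: 5.0%, 4.9%, 3.9%, 2.6%
- linear model with the strata: 5.0%, 5.3%, 4.8%, 4.5%

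The non-parametric branch therefore behaves like the t-test, and including the strata brings the size back to about 5%.

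**Limit of these figures.** The SDs describe the six-month score, whereas the primary outcome is change from baseline. The R² that matters is the one for that change.

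**The case against.** The article does not say that setting and gender will be ignored. It plans stratified and multivariate analyses, nothing excludes the two factors from them, and gender could well count as relevant given the article's own reasoning. This stands: the point concerns the named tests and the missing statement of which analysis is primary.

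The assumed R² may be too high. No prognostic reason is given for setting, and a constant difference in HECSI level between settings or genders cancels in a change score. This also stands. At R² = 0 the unadjusted test loses nothing.

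A reader might go further and infer that covariates will be picked after the data are seen, by an unblinded investigator, to favour the programme. The documents do not support that. They do not say when the choice is made, and a covariate list is commonly left to an analysis plan, which is not shown here. As a worst case, taking the smallest p-value over all 16 models from four confounders would raise the size from 5% to about 8.5%, 11% or 14% if each explained 2%, 5% or 10% of variance (assumed). The article describes no such procedure. That risk would also run in the opposite direction to the effect of omitting the strata, so the two should not be merged.

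A reader might also infer that setting is mixed up with the treatment contrast, because nurses and the investigator deliver the programme in setting A and a supervised health care assistant in setting B. Randomisation is within setting, so setting is not confounded with arm. The effect could differ between settings, but reporting an interaction is a preference, not the correction of an error.

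**Conclusion.** The point holds as a modest improvement at no cost. The named tests do not reflect the stratified randomisation, and the text does not commit any primary analysis to doing so. For an assumed R² of 0 to 0.20, the nominal 5% test runs at 5.0% down to 2.8%, intervals are 0% to 11.8% wider than needed, and at 150 per group about one point of power or less is lost. The direction is conservative throughout, so a positive result would not be put in doubt. That the strata are left out of the named tests is plain from the text; the size of the effect is not, because it rests on an R² that the documents do not supply.

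**What to change.** - **Primary comparison:** state that change in HECSI is compared between arms in a linear model with setting, gender and baseline HECSI as covariates. With baseline in the model, the treatment estimate is the same whether the response is the change or the six-month score, so the stated primary outcome need not change.
- **Secondary scores (DLQI and VAS):** include setting and gender in the same way. Where a rank test is kept, use one stratified by setting and gender.
- **Dichotomous outcomes:** use a Mantel-Haenszel test stratified by setting and gender, or a logistic model that includes them.
- **Other adjustment:** label analyses adjusted for further baseline questionnaire items as supportive.

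The cost is analysis wording only. Setting and gender are the randomisation strata, and HECSI is scored before randomisation, so no new data are needed and the sample size does not change.

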### Participants

Consecutive inclusion to the trial is performed. As soon as an individual is referred to treatment at the dermatologist due to ‘hand eczema’, an information letter is posted inviting the patient to participate in the trial. At inclusion, i.e. at first medical consultation at the dermatologist, signed, written informed consent is obtained. An objective evaluation of the present hand eczema is performed prior to an individual randomisation to either conventional information or to guidance according to the intervention. To enhance external validity of the trial, inclusion criterions are wide.

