### Primary outcome

#### Objective severity of hand eczema

The primary outcome variable is the change from baseline (T_0_) to follow up in objectively assessed disease severity, which is evaluated clinically by a member of the intervention team. The assessment relies on the Hand Eczema Severity Index (HECSI) which is a validated scoring system developed to quantify severity of hand eczema. HECSI is a visual medical assessment and subjective symptoms of the patient, e.g. itch or pain are not included 
[31]. Inter-rater variability in the present trial will be evaluated by random checks where patients are scored twice independently and by different assessors.

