### Blinding

The trial complies with usual clinical practice and the involved health professional actors will be the investigator and the members of the intervention team. It has been judged not to be feasible to maintain a fully blinded design throughout the trial. An effort is made to prevent performance bias by making the HECSI-scoring prior to randomisation. The HECSI scores are then removed from the participants’ data file to make the outcome assessment as blinded as possible. Also, when measuring primary outcome at six months follow-up, attempts are made to randomly allocate the member of the team, who does the HECSI-scoring. Hence, the participant may have been included by one member of the team; have been counselled by another; and have had final outcome assessed by a third member of the intervention team.

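### The stated selection-bias check rests on demographics and names neither baseline HECSI nor arm, so loss that tracks baseline severity differently by arm could bias the unadjusted change-score comparison without showing

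*Protocol article*

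**What the plan says.** All references are to the protocol article.

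- **Check for selection bias (Statistical methods).** The sentence opens with "Data from patients who refused to participate" and goes on: "dropouts, and loss-to-follow-up participants will be entered to an analysis based upon demographics in order to consider selection bias". Baseline HECSI and allocated arm are not mentioned.
- **Baseline severity (Randomisation).** "A baseline objective evaluation of hand eczema severity is carried out prior to the individual randomisation". The Participants section says the same, so every randomised patient has a score. Under Blinding, "The HECSI scores are then removed from the" participants' data files to help blind the later assessment. They must still be kept, because the outcome needs them.
- **Primary outcome (Objective severity of hand eczema).** "The primary outcome variable is the change from baseline" to follow-up in HECSI.
- **Analysis (Statistical methods).** Between-group differences in ordinal data are tested by t-test or a non-parametric test. Multivariate analyses and stratification for confounders are also planned, with no covariates named. For intention to treat, "all participants will be included in the analysis irrespective of compliance with the intervention protocol".

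**The concern.** The Measurement section lists demographics separately from medical history, predisposing factors and exposures, and HECSI is a separate clinical score. A check on demographics therefore does not, on its wording, look at severity.

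The article gives reasons why attendance at six months might relate to severity and to arm:

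- Need for hospital admission during follow-up is an exclusion criterion.
- Some patients are expected to be discharged before six months and others to need longer treatment (Trial duration).
- Intervention patients have nurse consultations and a website or hotline (Trial intervention). Controls receive information sheets at medical consultations and allergy tests (Conventional information) and are offered the counselling at the end of the trial (Risk/benefits).

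These are inferences about attendance, not facts stated in the article. If they hold, the patients who return differ in baseline severity between arms. The change score then differs between arms for that reason alone, while a table of age, gender and education may look balanced. The bias can run in either direction, depending on who is lost.

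**Working it through.** The article gives no figure for attrition bias, so there is none to reproduce. Its planned effect does reproduce: 11 × (1 − 0.30) = 7.7, a difference of 3.3 points.

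**Inputs from the article:** 150 per arm; mean baseline HECSI 19.9 (from the previous study it cites); control six-month SD 9.0.

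**Assumed inputs:** baseline SD σb of 12 or 16; baseline to six-month correlation ρ of 0.3, 0.5 or 0.7; right-skewed (log-normal) baseline; 20% loss per arm. The 20% lies within the margin in the sample size: 87 × 1.15 = 100, and 1 − 100/150 = 33%.

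**Step 1: shift in baseline among completers.** Suppose one arm loses 35% of patients below the median baseline and 5% of those above it (20% overall), and the other loses 20% at random. Completers in the first arm then have a mean baseline that is too high by

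(0.95 − 0.65)/(0.95 + 0.65) × h = 0.1875 × h,

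where h is half the gap between the means above and below the median. For a log-normal baseline, h = 19.9 × (2Φ(s) − 1), with s² = ln(1 + σb²/19.9²).

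- σb = 12: s = 0.557, h = 8.41, shift 1.58
- σb = 16: s = 0.706, h = 10.35, shift 1.94

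**Step 2: bias in the change score.** The regression of change on baseline has slope ρ × 9/σb − 1. The bias in size is therefore (1 − ρ × 9/σb) × shift. With the mirror-image pattern in the other arm it doubles. With the same pattern in both arms it cancels.

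**Step 3: false-positive rate with no true effect.** The standard error is SDc × √(2/120), with SDc = √(σb² + 81 − 18ρσb) and 150 × 0.8 = 120 completers per arm. The two-sided 5% rejection rate is Φ(−1.96 + bias/SE) + Φ(−1.96 − bias/SE).

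**Step 4: precision.** The ratio of the standard error with baseline as covariate to that of the change score is 9√(1 − ρ²)/SDc.

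| σb | ρ | Bias, one arm | Type I | Bias, opposite | Type I | SE ratio |
|---|---|---|---|---|---|---|
| 12 | 0.3 | 1.22 | 12% | 2.44 | 32% | 0.68 |
| 12 | 0.5 | 0.99 | 11% | 1.97 | 29% | 0.72 |
| 12 | 0.7 | 0.75 | 10% | 1.50 | 27% | 0.75 |
| 16 | 0.3 | 1.61 | 12% | 3.23 | 35% | 0.54 |
| 16 | 0.5 | 1.39 | 12% | 2.79 | 34% | 0.56 |
| 16 | 0.7 | 1.18 | 12% | 2.35 | 35% | 0.55 |

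Simulation of null trials over the same ranges of loss, SD and correlation gave about 0.8 to 1.5 points (one arm), 1.6 to 3.1 (opposite) and about 0 (same pattern). Baseline adjustment left at most about 0.2 points.

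**Step 5: would the stated check notice?** A second simulation used 150 per arm, normal scores, baseline SD 15, a true difference of −3.3, about 18% loss, log-odds of loss of 0.7 per SD of baseline (0.5 in the same-pattern case), and a demographic variable unrelated to HECSI.

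| Pattern of loss | Mean completer difference in change | Demographic check flags | Baseline HECSI, arms pooled | Baseline HECSI, by arm |
|---|---|---|---|---|
| One arm only | −1.8 to −2.0 | 4–6% | 56–63% | 80–85% |
| Opposite by arm | 0.0 to −0.9 | 4–7% | 5–7% | 94–97% |
| Same in both arms | −3.0 to −3.2 | 5–6% | 89–90% | 74–78% |

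For the demographic check, 4–7% is chance level. With opposite patterns even baseline HECSI shows nothing unless it is compared by arm. A model with baseline HECSI (and its interaction with arm) returned −3.3 to −3.4 throughout.

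**The case against.** The strongest reply is that the sentence describes a descriptive aid to interpretation, and that demographics are a sensible common basis because it also covers refusers, for whom the article provides no HECSI. That stands for refusers. It does not explain leaving severity out for randomised patients.

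Four stronger readings are tempting, and the article does not support them:

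- **Demographics will be the only basis.** The sentence does not exclude other variables, and the planned multivariate analyses might include baseline HECSI. The point is only that the article names demographics and not HECSI or arm.
- **Arm-specific loss would go unseen.** Allocation is known and CONSORT reporting is promised, so the numbers lost per arm should be visible. What the stated check would not show is how severe those patients were at baseline.
- **Missing outcomes will go uncorrected, and intention to treat becomes a completers' analysis.** The article gives no rule for a missing six-month HECSI, but imputation and sensitivity analyses are commonly left to a full protocol or SAP, neither of which is shown. This is not part of the point.
- **The trial will be biased.** That needs loss to depend on severity differently by arm. Controls also have medical consultations and the offer of counselling at the end, so retention may be similar. With a shared pattern the bias is close to zero.

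It is also fair that demographics may track severity to some degree; Step 5 assumes that they do not.

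**Conclusion.** The point holds in a limited form. For randomised patients the stated basis of the selection-bias check is poorly chosen, since a more informative variable is already held for all of them. The stated t-test or non-parametric comparison of change scores is also open to bias if baseline-dependent loss differs by arm.

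The size is conditional: about 0.8 to 1.5 HECSI points with dependence in one arm, or 24% to 45% of the planned 3.3 (0.8/3.3 and 1.5/3.3), roughly double with opposite patterns, and near zero with a shared pattern. These figures rest on the assumed loss rate and pattern, baseline SD, correlation and skewness, and show what could happen, not what is expected.

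The change is worth making because it is cheap and also improves precision. It is not a fatal flaw.

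**What to change.** 1. For randomised patients, compare completers with non-completers on baseline HECSI as well as demographics, separately by arm.
2. Keep the demographic comparison for patients who refused, and report it apart from loss after randomisation.
3. Estimate the primary between-group difference at six months by ANCOVA with baseline HECSI as covariate. This removes bias from loss that depends on baseline HECSI, provided the model for baseline is adequate; an arm-by-baseline term can be checked. Under the assumptions above, the standard error falls to about 0.54 to 0.75 of that of the change score.

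The cost is a little extra analysis and no new data collection. Loss that depends on the unobserved six-month score would not be removed by these steps.
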